### Sample size

According to the database used to assess the French version of the QoR-15 that included 72 patients undergoing gynecologic, digestive, or urologic major surgery, the mean QoR-15 score was 97 at 24 h after the surgery, with a standard deviation of 16. A difference of at least 8.0 points in the score is considered clinically significant [30]. The OFA will thus be superior to the standard of care if the mean QoR-15 is at least 105. Considering a type I error risk of 0.05 in two-sided test and a power of 0.8, the estimated number of patients needed is 126 (63 patients in both groups). Considering that data will not be available for ten percent of the patients (e.g., surgery canceled, lost in follow-up, consent withdrawal) regarding the primary outcome, we plan to include 140 patients.

### Follow-up

Nine visits are scheduled for all patients enrolled in the study. The plan summarizing the follow-up visits is presented in Fig. 2. The time T0 (hour 0/day 0) is the time of the surgical incision. The following data will be recorded at inclusion: demographic data, weight and height, ASA physical status classification, surgery type, and comorbidities. The SORT classification will also be recorded.

Perioperative surgical and anesthetic data will be recorded, including total dose of each medication. The anesthesiologist and the surgeon will also grade their satisfaction concerning the anesthesia.

In PACU, the total dose of pain medications, the occurrence of any complication, including postoperative nausea and vomiting (PONV), numerical pain rating scale, and PACU length of stay (in hours) will be recorded. In the ward visits (at 24, 48, and 72 h after the surgery), we will record the following data: QoR-15 questionnaire, maximal numerical effort pain scale, the occurrence of complications (using the POMS classification), morphine consumption, bowel movement, adverse event, and patient satisfaction (only at 24 h after the surgery). The QoR-15 questionnaires will be completed by the patient himself whenever possible, who could be helped by a nurse blinded to the assignment group, or by phone if the patient has returned home.

At 7 days, we will collect the morphine or equivalent daily consumption and the occurrence of surgical revision. The following data will be recorded at the hospital discharged visit (or 30 days after surgery): total length of stay and occurrence of in-hospital opioid side effects. A phone call to the patient will be made at 3-month to record the BPI, the DN-4, and the EQ-5D scores.

### Safety

Safety items will be collected during follow-up by the anesthesia team (during surgery) and participating investigators during other visits. Various events will be collected during the anesthesia and surgery (e.g., episodes of arterial hypertension or hypotension, episodes of bradycardia, a suspected hypersensibility reaction, and surgical complications). The occurrence of other adverse events that may be attributable to the protocol will be collected during the other follow-up visits (at 24 h, 48 h, 72 h, 7 days, and until discharge (censored at 30 days)). The occurrence of a serious adverse event will be collected at any time during the patient's follow-up (up to 3 months), whose imputability with one of the allocation groups will be discussed. Details of safety monitoring are available in the supplementary material.

### Data collection and study monitoring

Data will be entered into the electronic web-based case report form (eCRF on Ennov Clinical®). We will establish the database from the eCRFs.

A clinical research associate (CRA) mandated by the study sponsor will ensure the successful completion of the study, the collection of data, documentation, recording, and report, in accordance with the Standard Operating Procedures implemented in the Angers Hospital and in accordance with Good Clinical Practice, laws, and regulations.

The following items will be reviewed for every fifteen included patients:
Signed informed consent,Compliance with the study protocol and procedures that are defined,Quality of data collected in the case report form: accuracy, missing data, data consistency with the documents “source” (medical records, appointment books, original lab results, etc.).

After monitoring data on site, an automated check of the data entered will be made by the data management team based on the data validation plan signed by the coordinating investigator. Detected errors will lead to the issuance of requests for information and electronic correction.

### Statistical analysis

All analyses will be performed with R software (version 3.6.3). The main analysis will be in intention-to-treat and will include all randomized patients. Patients will be analyzed according to their randomization group. A per-protocol analysis will be performed as a sensitivity analysis to assess the main analysis robustness. A flow chart of all patients (Fig. 3) and descriptive statistics will be used to describe baseline characteristics. Data will be presented by their mean with standard deviation, median with interquartile range, number with the percentage of sample (%), or 95% confidence interval, according to their normal or non-normal distribution. We will report both absolute and relative measures for the comparisons between endpoints.

For the primary endpoint, we will use multivariate imputation for chained equations (with five imputations) via the mice package in R and perform a pooled-linear regression model, allowing us to perform an intention-to-treat analysis even if missing data. The covariates included in this analysis will be the allocation group, the type, and the surgery severity. This statistical method will also be used to analyze the QoR-15 at 48 and 72 h as secondary endpoints. To eliminate any influence of the phone evaluation, we will perform a sensitivity analysis just on the QoR-15 surveys collected in the ward.

We will also impute data for the analyses of other secondary endpoints: the rate of chronic pain patients at three months identified by the BPI via a logistic regression (same adjustment covariates) as well as for EQ-5D visual analog score via a linear regression (same adjustment covariates). The other endpoints will not be analyzed with the multiple imputation method. We reserve imputation for the endpoints included in the hierarchical scheme of the type I error management.

For each of the analyses involving the multiple imputation method, sensitivity analyses will be performed if the missing data rate for the endpoint of interest is greater than 10%. We will conduct an analysis only on the complete cases, as well as best-worst and worst-best case sensitivity analyses. For the best worst-case scenario, it is assumed that all participants lost to follow-up will have a beneficial outcome; and all those with missing outcomes in the other scenario will have a harmful outcome. For continuous outcomes, the beneficial outcome will be the group mean plus one standard deviation of the group mean, and the harmful outcome will be the group mean minus one standard deviation of the group mean [31]. To eliminate the potential risk of a violation of the normality, we will confirm the results for continuous variable implicating in the hierarchical scheme by sensitivity analysis using a semi-parametric approach with an ordinal model [32].

Concerning the pain evolution and morphine consumption variation, we will analyze those outcomes using a mixed effects linear regression model (fixed effect for the treatment arm, a fixed effect for the time frame, a fixed effect for each minimization factor, and a random effect for the patients). Hospital and PACU length of stays, as well as satisfactions (those of the surgeon, those of the anesthesiologist, those of the patient), will be compared using a linear regression model (allocation group and minimization factors as covariates). The proportion of complications of the POMS will be defined as a categorical variable (four levels: no complication, one complication, two complications, and more than 3 complications) and will be analyzed using a logistic regression model (allocation group and the minimization factors as covariates). The rate of patients presenting neuropathic pain, as well as the proportion of patients experiencing memorizations, will be compared by logistical regression models (allocation group and the minimization factors as covariates). Pain characteristics described by BPI and the proportion of patients in each of the five scales of EQ-5D will not be compared but only described.

All statistical analyses will be performed by two-sided tests. The signification cutoff will be a *p* value < 0,05 with 95% confidence interval.

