### Type I error management

We will manage the type I error in a sequential hierarchical manner (Fig. 4). We will test the first endpoint (i.e., QoR-15 at H24), and if the *p* value is less than 0.05, we will conclude that there is evidence of an effect. Then, we will test the following endpoint (i.e., QoR-15 at H48) using a significance level of 0.05. We will continue to test each endpoint of the hierarchical classification either up to the last endpoint (i.e., the quality of life by the EQ-5D visual analog scale at 3 months) or if we observe a non-significant result. Suppose a non-significant result (*p* value > 0.05) for one of the endpoints is observed. In that case, we will perform the following statistical comparisons in an exploratory manner without drawing any clinical conclusion.

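### Five imputations leave avoidable random noise in the primary p value that gates the test hierarchy; 50 to 100 would remove most of it at almost no cost

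*Protocol article*

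**What the plan says.** The Statistical analysis section of the protocol article fixes the number of imputations for the primary endpoint: "we will use multivariate imputation for chained equations (with five imputations) via the mice package in R". A linear regression is then pooled over the completed data sets. On the regression it adds: "The covariates included in this analysis will be the allocation group, the type, and the surgery severity". The same method is used for QoR-15 at 48 and 72 h. Chronic pain and the EQ-5D visual analog score at 3 months are also imputed, but no number of imputations is given for them.

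The Type I error management section sets a fixed sequence that starts with QoR-15 at 24 h, each step at 0.05. Confirmatory testing ends "if we observe a non-significant result", and everything after that is exploratory.

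The Sample size section allows for missing primary data: "Considering that data will not be available for ten percent of the patients". Complete-case and best/worst-case analyses are planned only when more than 10% of an endpoint is missing, and only as sensitivity analyses.

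**The concern.** A pooled estimate from a finite number of imputations, m, carries simulation error. Rerunning the same code on the same data with another seed gives a different estimate, standard error and p value. With m = 5 this error is not negligible, and here it enters the p value that controls the whole sequence. When the result lies near 0.05, the seed can decide whether the primary endpoint succeeds and whether later endpoints count as confirmatory. Another analyst repeating the analysis could reach the opposite conclusion from identical data.

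**Working it through.** **Inputs from the protocol article.** m = 5 and the regression covariates (Statistical analysis). From Sample size: a difference of 8.0 points, "with a standard deviation of 16", two-sided alpha 0.05, power 0.80, and 10% unavailable data. Allocation is 1:1.

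**Step 1: the plan's own figure.** n per arm = 2 × (1.960 + 0.842)² × 16² / 8² = 2 × 7.85 × 4 = 62.8, so 63 per arm and 126 in total. 126 / 0.9 = 140. The stated sample size reproduces.

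**Step 2: size of the noise by formula.** The Monte Carlo SD of the pooled estimate, in units of its standard error, is about √(λ/m), where λ is the between-imputation share of the variance. In the simulation below, λ was about 0.11 at 10% missing.
- m = 5: √(0.11/5) = 0.15
- m = 50: √(0.11/50) = 0.047
- m = 100: √(0.11/100) = 0.033

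Call the p value that unlimited imputations would give the limiting p. A limiting p of 0.04 corresponds to z = 2.054, which is 0.094 above the critical 1.960. The chance that noise alone crosses that gap is roughly:
- m = 5: 0.094/0.148 = 0.63, about 26%
- m = 50: 0.094/0.047 = 2.0, about 2%
- m = 100: 0.094/0.033 = 2.8, about 0.2%

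This understates the m = 5 figure, because with five draws the between-imputation variance is itself poorly estimated.

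**Step 3: simulation, conditional on the limiting p.** N = 140, SD 16, 10% missing. The regression contained arm, five surgery types and three severity levels (the protocol lists four). Imputation was proper normal-model imputation, pooled by Rubin's rules with small-sample degrees of freedom. Assumptions: missing completely at random, no auxiliary variables, evenly spread strata. Six data sets were each shifted to a target limiting p and re-imputed 1,000 times per m.

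Share of seeds giving p < 0.05:

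| Limiting p | m = 5 | m = 20 | m = 50 | m = 100 |
|---|---|---|---|---|
| 0.04 | 65% | 85% | 97% | over 99% |
| 0.05 | 46% | 48% | 49% | 50% |
| 0.06 | 27% | 14% | 5% | 1% |

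With m = 5 the share is 96% at a limiting p of 0.02 and 8% at 0.08. The zone in which the seed can matter therefore runs from about 0.02 to 0.08; with m = 50–100 it narrows to about 0.04–0.06. At a limiting p of 0.05, the 5–95% range of p across seeds is 0.028–0.097 with m = 5 and 0.044–0.057 with m = 100.

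**Step 4: how often this would arise.** Chance that two seeds disagree on significance, same assumptions, 10% missing:

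| True difference | m = 5 | m = 50 | m = 100 |
|---|---|---|---|
| 8 points | 5.9% | 1.4% | 1.4% |
| 5.6 points | 7.7% | 2.2% | 1.3% |
| 0 | 2.1% | 0.8% | 0.3% |

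Repeat simulations at 8 points gave 6.3% and about 7% with m = 5, and about 1–2% with m = 50–100.

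**Step 5: operating characteristics.** Simulated type I error with m = 5 was 0.044 (0.051 in a repeat). Power at 8 points was 0.77 with m = 5 and about 0.78 with m = 20–100.

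**The case against.** The strongest reply is that five imputations give a valid analysis. Type I error holds, the estimate is unbiased, and about one point of power is lost. A result well away from 0.05 is unaffected, and any finite m leaves some seed dependence at the threshold: at a limiting p of exactly 0.05, even m = 100 splits the seeds evenly. All of this stands, and it limits the point to reproducibility.

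The noise may also be smaller than computed. The 10% allowance covers cancelled surgery and consent withdrawal, some of which may precede randomization, and the questionnaire can be completed by phone. At 5% missing with m = 5, 76% of seeds reach p < 0.05 at a limiting p of 0.04, against 65% at 10% missing. An imputation model with a good predictor would also help: with one fully observed auxiliary correlated 0.7 with the outcome (an assumption), disagreement at 10% missing fell from 6.3% to 3.5%. This reduces the size of the problem but does not remove it.

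A reader might infer more than the article supports:
- **That imputation uses only arm, surgery type and severity**, and so merely reproduces the complete-case estimate with added noise. The covariate sentence follows the mention of the pooled regression, and the next paragraph of that section treats the same set as adjustment covariates. It describes the analysis model. The imputation predictors are not listed and may be in the analysis plan, which is not shown.
- **That no seed is fixed.** This too may be in the analysis plan. A fixed seed would prevent choosing among seeds but would not reduce the noise of m = 5.
- **That five imputations also apply at 3 months**, or that missingness will be 20–30%. The article states neither.

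**Conclusion.** The point holds as a modest one about reproducibility. The article itself fixes m = 5 for the p value that opens the hierarchy. At its own 10% allowance, that leaves about a 6–7% chance at the design difference, and about 2% under no effect, that two seeds give opposite primary conclusions. With 50–100 imputations these figures are about 1–2% and under 1%. They assume data missing completely at random and no auxiliary variables: more missing data would raise them, and good auxiliary variables would lower them. The planned sensitivity analyses are not a safeguard, because they are not triggered at 10% or below and would not replace the gating p value. Nothing here suggests a biased or invalid primary test.

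**What to change.** In the Statistical analysis section, replace five with 100 imputations (at least 50) for the endpoints in the hierarchy, and run them under a pre-specified seed. Leave the pooled regression and its covariates as they are. If the imputation model would otherwise contain only arm, surgery type and severity, add QoR-15 at the other time points and other outcomes already collected, such as effort pain, POMS complications and morphine consumption; this would reduce the noise further. The cost is one sentence and seconds of computing. No patient, visit or data item is affected.

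### The best-worst and worst-best analyses are defined by scenario, not by arm; this contradicts their names and, read literally, understates sensitivity to missing data

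*Protocol article*

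**What the plan says.** All references are to the protocol article.

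- **Statistical analysis, names.** Endpoints analyzed with multiple imputation get a complete-case analysis "as well as best-worst and worst-best case sensitivity analyses".
- **Statistical analysis, definition.** Under the best-worst label, "it is assumed that all participants lost to follow-up will have a beneficial outcome; and all those with missing outcomes in the other scenario" are given a harmful one. Neither half names the OFA or the control arm.
- **Statistical analysis, values.** The favorable value on a continuous scale is fixed as follows: "the beneficial outcome will be the group mean plus one standard deviation of the group mean". The unfavorable value mirrors it, lying the same distance below.
- **Statistical analysis, trigger.** These "sensitivity analyses will be performed if the missing data rate for the endpoint of interest is greater than 10"%.
- **Sample size.** The calculation uses SD 16 and a difference of 8.0 points, and arrives at 126 evaluable patients, 63 per group. Then: "Considering that data will not be available for ten percent of the patients" for the primary outcome, "we plan to include 140 patients".

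The imputed endpoints named in the text are QoR-15 at 24, 48 and 72 h, chronic pain at three months (binary, logistic regression) and the EQ-5D visual analog score.

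**The concern.** A best-worst case takes its force from opposite assumptions in the two arms: missing patients do well in one and badly in the other. The printed definition contrasts two scenarios instead, and within each scenario every missing patient goes in the same direction. Each arm's missing values are placed one SD above (or below) that arm's own mean, so both arm means move together and most of the movement cancels in the difference.

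The other sensitivity analyses listed (per-protocol, ward-only questionnaires, complete cases, ordinal model) do not assign favorable or unfavorable outcomes to missing patients. These two scenarios are therefore the only listed check on how far the result depends on what happened to those patients. If they are programmed as printed, a fragile result could be reported as robust.

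**Working it through.** **Inputs.** SD 16, difference 8, two-sided alpha 0.05, power 0.80, 126 evaluable, 140 randomized and 10% unavailable (Sample size); 1:1 allocation, so 70 per arm (Randomization and blinding).

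**The plan's own figure.** n per arm = 2 × (1.96 + 0.84)² × (16/8)² ≈ 62.8, so 63, and 126 in total. 126/0.9 = 140. Both figures reproduce. The plan therefore expects 14 of 140 missing, exactly 10.0%.

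**Continuous endpoints.** Let d be the observed OFA-minus-control difference, s a common SD, and f1 and f2 the missing fractions in OFA and control. Setting an arm's missing values to its own mean ± s moves that arm's mean by ± s × f.

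- As printed (same direction in both arms): d ± s(f1 − f2).
- Opposite direction by arm: d ± s(f1 + f2).

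With s = 16, d = 8 and 70 per arm:

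| Missing OFA / control | Overall | As printed | Opposite by arm |
|---|---|---|---|
| 7 / 7 | 10.0% | 8.00 / 8.00 | 11.20 / 4.80 |
| 8 / 8 | 11.4% | 8.00 / 8.00 | 11.66 / 4.34 |
| 10 / 5 | 10.7% | 9.14 / 6.86 | 11.43 / 4.57 |
| 12 / 3 | 10.7% | 10.06 / 5.94 | 11.43 / 4.57 |
| 14 / 14 | 20.0% | 8.00 / 8.00 | 14.40 / 1.60 |

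For example, at 10% in each arm the opposite shift is 16 × (0.10 + 0.10) = 3.2; at 20% it is 16 × (0.20 + 0.20) = 6.4. The smallest difference that reaches significance with 63 per arm is about 1.98 × 16 × √(2/63) = 5.6.

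**Effect on conclusions.** This uses an unadjusted two-sample t test after filling in the values, with 8 missing per arm, so the trigger is met.

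- Observed difference 8: as printed, p = 0.003 in both scenarios. Opposite by arm, worst-best gives 4.34, p about 0.11.
- Observed difference 6: as printed, p = 0.027 in both scenarios. Opposite by arm, worst-best gives 2.34, p about 0.38.

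**Chronic pain (binary).** With the same missing fraction f in both arms and observed risks p1 and p2:

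- As printed: both scenarios give a risk difference of (1 − f)(p1 − p2).
- Opposite by arm: (1 − f)(p1 − p2) ± f.

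The article gives no expected rates, so take 20% v 30% with f = 0.10 as an assumption. The observed risk difference is −10 points and the odds ratio 0.58.

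- All beneficial: 18% v 27%, risk difference −9, odds ratio 0.59.
- All harmful: 28% v 37%, risk difference −9, odds ratio 0.66.
- Best-worst by arm: 18% v 37%, risk difference −19.
- Worst-best by arm: 28% v 27%, risk difference +1.

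**Trigger.** 14/140 = 10.0% is not greater than 10%. The first count that triggers is 15/140 = 10.7%. If each patient were independently missing with probability 0.10 (an assumption), 15 or more would be missing in about 43% of trials.

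**The case against.** The strongest reply is that this is a drafting slip. The names already mean opposite assignment by arm, and the beneficial and harmful halves both follow the best-worst label, so the word scenario may simply stand for group. That is plausible. A reader might infer that the trial will certainly run two checks that report robustness whatever the data; the article does not support that. Even on the charitable reading, though, the sentence does not say which arm is favored and does not spell out the reverse case, so the rule still has to be rewritten.

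Other stronger readings also fail:

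- **The two arms get identical values.** They do not, because each arm uses its own mean. The cancellation is exact only with equal missingness and equal SDs.
- **The effect is zero for every imputed endpoint.** It is not. For chronic pain the risk difference shrinks by the factor (1 − f) and the odds ratio moves somewhat.
- **The step is a standard error.** The phrase about the SD of the group mean could be taken as 16/√63 = 2.0, which would cut the opposite-arm shift at 10% from 3.2 to 0.4 points. This is strained, since the Sample size section uses standard deviation for the patient-level 16. It is loose wording to tidy, not an error to charge.
- **The analyses will never run.** The 10% trigger is a prespecified threshold, applied endpoint by endpoint, and may well be exceeded. The 10% allowance in the Sample size section concerns the primary outcome only.
- **Correct assignment would bound the effect.** Mean ± 1 SD is a stress test, not an extreme bound, in either version.

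**Conclusion.** The definition contradicts the names of the analyses. Read literally, it understates sensitivity to missing data: a shift of 16 × (f1 − f2), zero under balance, in place of 16 × (f1 + f2), which is 3.2 points at 10% missing per arm. In the examples, that separates an unchanged significant result from a worst-best result that is no longer significant.

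The figures assume SD 16 in both arms, 70 patients per arm and no covariate adjustment. The planned regression on the minimization factors would change them somewhat, but not the pattern.

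This should be fixed. It is more than a missing detail, because a rule is stated and would mislead if followed. It is less than critical, because these are conditional sensitivity analyses: the multiple-imputation primary estimate, the sample size and the hierarchical testing rule do not depend on them.

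**What to change.** Replace the definition with one stated by arm:

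- **Continuous endpoints, best-worst:** missing OFA = observed OFA mean + 1 SD of individual scores in that arm; missing control = observed control mean − 1 SD of individual scores in that arm. **Worst-best:** the reverse.
- **Chronic pain, best-worst:** missing OFA = no chronic pain; missing control = chronic pain. **Worst-best:** the reverse.

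Optionally, run these and the complete-case analysis whenever any data are missing for the endpoint, since the present trigger is not met at exactly the planned 14 of 140. This is a low-cost improvement, not the correction of an error.

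The cost is a few sentences in the analysis plan and a few extra model fits, with no effect on patients or sites. The change should be made before outcomes are seen by arm, so that the choice of definition cannot be driven by the results.

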#### Secondary outcomes

In order to confirm the impact of the OFA protocol on postoperative recovery, we will also measure the QoR-15 score at 48 h and 72 h after the surgery in all patients. We will evaluate the pain during effort (mobilization, cough or physiotherapy sessions) and the number of postoperative complications according to the POMS (postoperative morbidity survey) classification [27], assessed up to 72 h after the surgery. The postoperative consumption of morphine-equivalent will also be compared between the two groups. The lengths of stay in PACU and in the hospital will be measured.

We will compare the patient tolerance to the allocated protocol with the assessment of the hemodynamic status (intra-operative use of vasopressor or cessation of one of the drugs for hemodynamic purposes), heart-rhythm (< 35 or > 140 beats per minute for more than 30 s), and anaphylactic reactions. Another secondary outcome is the respect of the allocated protocol by the anesthesia team: OFA protocol will be considered complete if at least two of the following drugs are used between ketamine, lidocaine, clonidine, and magnesium sulfate, and if no intraoperative opioids are used; the standard group will be considered complete if lidocaine, clonidine, or magnesium sulfate are not used intra-operatively. The surgeon’s and anesthesiologist’s satisfactions concerning the anesthesia will be assessed after the surgery according to a numerical scale (rated from 0 to 10). We will also compare the patient satisfaction of anesthesia at 24 h via a numerated scale from 0 to 10 (0 = not satisfied and 10 = totally satisfied) and the presence or absence of intra-operative memorization.

Three months after surgery, a phone interview will be conducted to evaluate the chronic pain using the Brief Pain Inventory (BPI) [28] in its French short version, the quality of life using the French EQ-5D-3 L questionnaire (available on request on https://euroqol.org/), and the rate of neuropathic pain diagnosed using the DN-4 questionnaire [29].

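### The mixed model for pain evolution and morphine variation has no arm-by-time term, so it gives only a time-averaged difference and cannot show whether the course differs between arms

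*Protocol article*

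**What the plan says.** The Statistical analysis section introduces the model with the words "Concerning the pain evolution and morphine consumption variation, we will analyze those outcomes using a mixed effects linear regression model". It then lists the terms: a "fixed effect for the treatment arm, a fixed effect for the time frame, a fixed effect for each minimization factor, and a random effect" at patient level. There is no interaction between arm and time, and the article gives no time-specific contrast for these two outcomes anywhere else.

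Under Follow-up, effort pain and morphine consumption are recorded at three ward visits, at 24, 48 and 72 h. For morphine there is one more time: "At 7 days, we will collect the morphine or equivalent daily consumption". The article does not say whether that value enters the mixed model.

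The Secondary outcomes section is worded more loosely. Effort pain is to be evaluated up to 72 h, and for morphine "The postoperative consumption of morphine-equivalent will also be compared between the two groups".

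Imputation is reserved for endpoints in the hierarchical testing scheme. Pain and morphine are not among the imputed endpoints, so by that rule they lie outside the hierarchy.

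**The concern.** The label and the model do not match. *Evolution* and *variation* suggest that the arms will be compared on how pain and consumption change. With additive arm and time effects, the time coefficients describe a course shared by both arms, and the arm coefficient is one vertical shift between two parallel profiles. This follows from the listed terms and needs no assumption about the data. Because the article spells the terms out, it is also more than a detail left to an analysis plan.

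Two things are at stake. A statement that pain or consumption evolved differently, or similarly, under opioid-free anesthesia could not be supported by this model. And if the true difference varies over time, the single coefficient may understate it at the times when it is largest.

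**Working it through.** **The plan's own figure.** With a difference of 8, SD 16, two-sided alpha 0.05 and power 0.80 (Sample size section), n per arm = 2 × (1.960 + 0.842)² × 16² / 8² = 62.8, so 63 per arm and 126 in total. Then 126 / 0.9 = 140. Both figures reproduce, and this point disputes neither.

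**Inputs from the article.** 63 evaluable patients per arm; T = 3 ward time points; two-sided alpha 0.05.

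**Assumptions, not in the article.** A 24 h difference of 0.5 SD (the standardized effect of the primary endpoint, 8/16, borrowed for scale); within-patient correlation ρ from 0.3 to 0.7; equal SD at each time; complete data.

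**Formulas.** In a balanced additive random-intercept model, the arm coefficient is the mean of the time-specific differences. In SD units:

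- SE of the arm coefficient = √[(1 + (T − 1)ρ)/T] × √(2/63)
- SE of a difference at one time = √(2/63) = 0.178
- Power ≈ Φ(difference/SE − 1.96)
- Joint arm-by-time test: chi-square on T − 1 df, noncentrality 63 × Σ(difference − mean difference)² / [2(1 − ρ)]

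**Effect at 24 h only (0.5, 0, 0).** The arm coefficient is 0.5/3 = 0.167.

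- ρ = 0.3: SE = √(1.6/3) × 0.178 = 0.130; 0.167/0.130 = 1.28; power 25%.
- ρ = 0.7: SE = √(2.4/3) × 0.178 = 0.159; 0.167/0.159 = 1.05; power 18%.
- 24 h contrast: 0.5/0.178 = 2.81; power 80%.
- Joint test: Σ = 0.167, so the noncentrality is 7.5 at ρ = 0.3 and 17.5 at ρ = 0.7; power 69% and 97%.

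**Three assumed patterns, T = 3** (power for ρ = 0.3 / 0.5 / 0.7):

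| Difference at 24/48/72 h (SD) | Arm coefficient (SD) | Power, arm coefficient | Power, 24 h contrast | Power, joint interaction test |
|---|---|---|---|---|
| 0.5 / 0 / 0 | 0.17 | 25 / 21 / 18% | 80% | 69 / 84 / 97% |
| 0.5 / 0.25 / 0.125 | 0.29 | 61 / 52 / 45% | 80% | 35 / 47 / 70% |
| 0.5 / 0.5 / 0.5 | 0.50 | 97 / 93 / 88% | 80% | 5% (no interaction present) |

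**Simulation check.** 200 fitted mixed models at ρ = 0.5 with the 24 h-only effect gave a mean additive coefficient of 0.18 SD and rejection in 25.5% of runs. The closed form gives 0.167 and 21%, which is within simulation error (standard error of the rejection rate about √(0.21 × 0.79/200) = 2.9 points). The interaction model recovered the 24 h difference at 0.50 SD.

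**If the day-7 morphine value enters the model (T = 4).** A 24 h-only effect becomes 0.5/4 = 0.125 SD, with 12–17% power for the arm coefficient.

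**The case against.** The strongest reply is that the Secondary outcomes section sets no hypothesis about trajectories. It asks for pain to be evaluated and morphine to be compared, and *evolution* and *variation* may simply label repeated measurements. The arm coefficient answers that looser question validly. This stands. A reader might infer that the model fails to answer the question the plan sets, but the documents support only a mismatch between the outcome labels and the model.

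A reader might also infer that the effect must be confined to the first 24 h, so that the model averages it away, or that an early benefit with a late rebound would be hidden. The article supports neither. It stops ketamine before the end of surgery and lidocaine after 1 h in the PACU. But it also tests QoR-15 at 48 h, follows patients to 3 months, and says clonidine was chosen partly because its benefits seem to last longer. No section describes a rebound. An early-only effect is an assumption, and even then one third of it remains in the estimate.

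The additive model also has a real advantage. If the effect is constant, it has 88–97% power against 80% for a contrast at one time.

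Finally, per-time contrasts bring multiplicity. With Bonferroni over three contrasts the critical value is 2.39, and the 24 h power becomes Φ(2.81 − 2.39) = 66%. That is a reason to read the contrasts as exploratory. It does not make the additive model able to describe a course.

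**Conclusion.** The point holds in a limited form. The listed model estimates a time-averaged arm difference and can neither show nor test a difference in course, although the outcomes are named as evolution and variation. That part is structural and certain.

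The dilution is conditional. For a 0.5 SD effect at 24 h only, with 63 per arm, ρ of 0.3 to 0.7 and three time points, the estimate is one third of the 24 h difference, with 18–25% power. For a halving effect it is 58% of the 24 h difference, with 45–61% power. For a constant effect there is no dilution, and the additive model is preferable. None of these patterns or correlations comes from the article.

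The consequence is confined to secondary outcomes outside the hierarchy. QoR-15 is analyzed separately at 24, 48 and 72 h and does not share the problem.

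**What to change.** Add an arm-by-time interaction to the mixed model, with time as a categorical factor. From that one model, report:

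- the adjusted arm difference with 95% CI at 24, 48 and 72 h, and at day 7 for morphine if that value is included (the plan should say whether it is);
- the joint interaction test as the test of evolution;
- the time-averaged arm difference as the single overall comparison, so that the strength of the additive analysis under a constant effect is largely kept.

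If the sponsor wants only the time-averaged difference, the plan should name it as the target and drop the words *evolution* and *variation*.

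The cost is one model term, a few degrees of freedom, and several contrasts that should be declared exploratory. The joint test has modest power against a gradual decline (35–70% above), so a non-significant result should not be read as showing parallel courses. Data collection, sample size and the primary analysis do not change.
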